### Eligibility criteria

Participants providing written informed consent further need to meet the following inclusion criteria: (a) age 18 or above, (b) enrolled in university or college, (c) sufficient knowledge of German language (assessed via capability to proceed through enrollment and screening process), (d) internet access, (e) moderate to low mindfulness (Freiburg Mindfulness Inventory FMI ≤ 37); this cutoff was chosen as it represents the medium value of the FMI in subjects from the general population [56]. Participants are excluded from the study if they are undertaking psychotherapy or any kind of mindfulness intervention at the time of the screening.

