### Setting/recruitment

Recruitment took place from May 2018 to April 2020. The main recruitment channel consists of circular e-mails sent out by more than 15 cooperating colleges in Germany, Austria, and Switzerland to all their students once every semester (for full list of cooperating colleges see StudiCare-Website [45]). Additionally, students are recruited via flyers and posters, social media, student unions, and student counseling. In the circular emails, students are informed about the StudiCare offers and are provided with a link to the StudiCare homepage [45], where they can obtain further information and register for the IMIs. Once registered, they receive an email with a link to the eligibility screening. Depending on which college participants attend, they are either allocated to a parallel local trial at Ulm University which combines StudiCare-M with on-site laboratory and psychophysiological measures [57] or to the present study (all other cooperating colleges). After successfully completing the screening, they receive an email with further information on the study as well as an informed consent form which they are required to send to the study team. When written consent is obtained and the pretest completed, another email with a link to the intervention is sent to participants randomized to one of the intervention groups. Participants are informed that StudiCare-M is not designed to replace psychotherapy, recommended to seek counseling/psychotherapy in case of distinctive mental health problems and provided with further treatment options and contact details. Participants of the WL will receive information on further study procedures as well as on alternative support options they can seek in case of deterioration of wellbeing during the waiting period.

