### Assessments and outcomes

Assessment takes place before (t0; baseline) as well as 4 weeks (t1; intermediate), 8 weeks (t2; post-treatment), and 6 months (t3; follow-up) after randomization. t1 is an intermediate assessment of a subset of outcomes (see Table 2). All data will be self-reported and collected via the online survey platform “Unipark” [64]. Blinding of outcome assessment will therefore not be possible. To reduce assessment dropout, an email reminder strategy is employed. Participants’ phone numbers are collected on a voluntary basis to have the possibility of reminding them of filling out the surveys. Additionally, a raffle of 10 20-Euro “Amazon” coupons will take place among completers of the t3-survey at the end of the study.

**Table 2 Tab2:** Outcomes and assessment points

Variables	Measurement	Screening	t0	t1	t2	t3

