### Statistical analyses

All data analyses will be performed after completion of data collection. Interim analysis is not considered necessary as in the context of IMIs, there are no known dangers or harms that could make a trial stop necessary. Analyses will be performed on an intention-to-treat basis. Procedures of imputation will be chosen based on patterns and mechanisms of missingness (e.g., by using multiple imputation). Additionally, per protocol analyses (based on the data of participants that completed at least 5 of the 7 core modules) will be performed to examine the impact of drop-outs on study results. Significance level for all analyses will be defined as alpha = .05. A blinded analysis of primary and secondary outcomes will be conducted by an independent researcher not otherwise involved in the execution of the study (MM).

The primary outcome FMI at t2 will be analyzed by means of linear regression models. Baseline and group will be defined as predictors. Secondary outcomes will be analyzed accordingly. Standardized mean differences with 95% confidence intervals will be calculated post-treatment and follow-up to analyze between-group effect sizes. To obtain the number of participants achieving reliable improvement in mindfulness (FMI), participants will be coded as responders and nonresponders according to the Reliable Change Index (RCI) for t2 and t3 [94]. Additionally, we will investigate potential negative effects on individual level by calculating the number of participants that display a reliable deterioration from t0 to t2 and t3 also using the RCI [95, 96]. For an exploratory examination of associations between adherence, subscription to SMS-coach, actual use of GoD, time spent practicing mindfulness exercises, and the primary outcome FMI at t2 regression analyses will be conducted.

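### Optional precision gain: the stated primary model adjusts FMI at t2 for the t0 score only, although each randomised participant should also have a pre-randomisation screening FMI

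*Protocol article*

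**What the plan says.** Statistical analyses: "The primary outcome FMI at t2 will be analyzed by means of linear regression models", and "Baseline and group will be defined as predictors". Secondary outcomes follow the same form.

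Assessments and outcomes identifies baseline with t0: "Assessment takes place before (t0; baseline) as well as 4 weeks (t1; intermediate". Table 2 lists the FMI in a Screening column and again, separately, at t0.

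Eligibility criteria requires "moderate to low mindfulness (Freiburg Mindfulness Inventory FMI ≤ 37", and explains that "this cutoff was chosen as it represents the medium value of the FMI in subjects from the general population". This cutoff is the only use of the screening score that the article states.

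The order of events is clear. Under Setting/recruitment the screening comes first, then consent and the pretest: "When written consent is obtained and the pretest completed, another email with a link to the intervention is sent". Under Randomization, allocation follows the baseline assessment. Both FMI scores therefore precede allocation. The interval between them is not given.

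**The concern.** The entry criterion and the primary endpoint use the same scale, and a participant cannot be enrolled without a screening score. A second complete, pre-randomisation reading of the outcome measure is thus already held, but the stated primary model does not include it.

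A single t0 score contains measurement error. Selection at FMI ≤ 37 narrows the range of true scores in the enrolled sample, which lowers the reliability of the t0 score there. A second fallible reading of the same construct can recover part of what is lost and reduce the residual variance of FMI at t2. Only precision is at stake, in the primary comparison and in FMI at t1 and t3.

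**Working it through.** **1. The plan's sample size.** From Sample size estimation: d = 0.40, α = 0.05, power 90%, ICC 0.02. The test is taken as two-sided, as stated for the original calculation.

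- n per group = 2(1.960 + 1.282)²/0.40² = 131.3, so 132 by normal approximation. The exact t-test gives 133, the original figure.
- With variance 1 − 0.02 = 0.98: 131.3 × 0.98 = 128.7, so 129, with power 0.901. This matches the stated figure.

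The 129 is reached without any reduction for baseline adjustment, so what t0 or screening FMI explains is a bonus on top of the planned 90%.

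**2. When a second score helps.** Let r0 be the t0–t2 correlation, rS the screening–t2 correlation and r0S the screening–t0 correlation.

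- Residual variance with t0 only: 1 − r0².
- With both: 1 − R², where R² = (r0² + rS² − 2·r0·rS·r0S)/(1 − r0S²).

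Examples without selection, r0 = 0.6 and r0S = 0.8:

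- rS = 0.60: R² = (0.72 − 0.576)/0.36 = 0.40; ratio 0.60/0.64 = 0.938.
- rS = 0.54: R² = (0.6516 − 0.5184)/0.36 = 0.37; ratio 0.63/0.64 = 0.984.
- rS = 0.48 = r0 × r0S: R² = 0.36; ratio 1, no gain.

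The gain vanishes when rS = r0 × r0S. Suppose each reading is a true score plus independent error with reliability ρ, the true scores correlate c between screening and t0, and stability from t0 to t2 is s. Then rS = ρcs, whereas r0 × r0S = ρs × ρc = ρ²cs. These are equal only if ρ = 1. The article gives α = 0.84 for the FMI, so under this model some gain is expected.

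**3. Size after selection at the cutoff.** None of ρ, c or s is in the article. Assumed: ρ = 0.70-0.84, c = 0.90-1.0, s = 0.7-0.9, normal scores, cutoff at the general-population mean. Simulated residual variances are shown as fractions of the t2 variance in the enrolled sample. Power at 129 per group and d = 0.40 is Φ(0.40/√(2v/129) − 1.96).

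| ρ | c | s | v, t0 only | v, both | Variance cut | SE cut | Power |
|---|---|---|---|---|---|---|---|
| 0.84 | 0.90 | 0.7 | 0.787 | 0.776 | 1.5% | 0.7% | 0.952 → 0.954 |
| 0.70 | 0.90 | 0.7 | 0.849 | 0.833 | 1.9% | 1.0% | 0.937 → 0.941 |
| 0.84 | 0.95 | 0.9 | 0.617 | 0.585 | 5.3% | 2.7% | 0.983 → 0.988 |
| 0.70 | 1.0 | 0.9 | 0.763 | 0.712 | 6.6% | 3.4% | 0.957 → 0.968 |
| 0.84 | 1.0 | 0.9 | 0.649 | 0.596 | 8.0% | 4.1% | 0.979 → 0.986 |
| 0.84 | 1.0 | 1.0 (extreme) | 0.496 | 0.423 | 14.8% | 7.7% | 0.995 → 0.999 |

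Worked row (0.84, 1.0, 0.9): √(2 × 0.649/129) = 0.1003 and 0.40/0.1003 − 1.96 = 2.03, so power is 0.979. With 0.596: √(2 × 0.596/129) = 0.0961 and 0.40/0.0961 − 1.96 = 2.20, so power is 0.986.

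**4. A check with correlations assumed directly.** With r0 = 0.5-0.7, r0S = 0.7-0.84, rS = 0.9-1.0 times r0 and the same truncation, the variance cut is 0.3-10%, the SE cut about 0.1-5%, and the power gain at most about 1 point. The ranges overlap.

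**5. Smaller effects.** With an assumed residual SD of 0.8 and a 6% variance cut, power at 129 per group moves from about 0.60 to 0.625 at d = 0.22 (the article's pooled effect for unguided interventions) and from 0.52 to 0.54 at d = 0.20.

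**6. Cost.** With 387 participants, residual degrees of freedom go from 387 − 4 = 383 to 382.

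**The case against.** The strongest reply is that nothing here is wrong. Regression on group and the t0 score of the same instrument is a standard, valid, prespecified analysis. Leaving out a second pre-randomisation score causes no bias, no type I error problem and no shortfall against the planned power. That stands in full, and it is why the point is only an optional refinement.

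A reader might infer that the screening score is discarded. The article does not say so. It names the predictors of the regression and leaves the imputation procedure to be chosen on patterns and mechanisms of missingness. The screening score may well serve there, and its absence from an imputation list is no finding.

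A reader might also take a gain of about 15% as the expected result. That needs a true score unchanged between screening and t0 and perfectly stable individual standing from t0 to t2, which sits poorly with a trial that looks for moderators of response. Screening, return of a consent form and the pretest are separate steps, so some drift is possible. The quoted α is internal consistency and not retest reliability, and errors shared between two closely spaced readings would shrink the gain. It could be nil if t0 already carried everything that the screening score tells about t2.

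Finally, only the FMI is listed at screening, so the change gives FMI outcomes a different model form from the other scales. Recruitment is complete, so expressing the gain as participants saved has no practical meaning here. Both remarks are fair.

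**Conclusion.** The point holds as an optional improvement of low severity. The stated primary model uses one of two pre-randomisation FMI scores that each randomised participant should have, and the second is a legitimate covariate that needs no new data.

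Under the stated assumptions, residual variance falls by roughly 1.5-8% and the standard error by about 1-4%. Power at d = 0.40 rises by about 1 percentage point or less, from a level already above 90%. The article supplies no screening–t0, t0–t2 or screening–t2 correlation, so the value cannot be fixed more closely. It does not support reading the planned analysis as biased, underpowered or in error on this account.

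**What to change.** In Statistical analyses, before unblinding, state that the FMI outcomes at t1, t2 and t3 are regressed on group, FMI at t0 and FMI at screening. Keep t0 as the reference for change scores and for the Reliable Change Index. Leave the model for the other secondary outcomes as it is.

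The article places all analyses after completion of data collection and assigns the primary and secondary outcomes to a blinded independent analyst, so the change can still be prespecified without knowledge of results. It costs one degree of freedom, a sentence of text, and a model form for FMI that differs slightly from that of the other secondary outcomes.

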#### Guidance and promotion of adherence

Participants randomized to the GoD version of the intervention receive support by an e-coach whenever they desire to. E-Coaches are trained and supervised (by HB, AK) psychologists that give semi-standardized feedback on demand within 2 working days, following an e-coach manual. Whenever participants have questions or wish feedback on their module input, they can contact their personal e-coach via the platform’s message function. Each participant receives a welcoming message by their e-coach as well as a short introduction how to use GoD in the first module. Feedback content is specific to participants’ assignments and includes positive reinforcement, motivation, and encouragement. Actual usage of GoD by participants is documented. Participants in the unguided version of StudiCare-M do not receive any guidance. However, they receive short standardized automated feedback messages after completion of each module to reinforce and motivate them to continue the intervention. In both groups, participants are sent automated standardized e-mails by the Minddistrict platform if they have not logged in for more than 7 days. There will be no special criteria for discontinuing or modifying allocated interventions. However, all participants allocated to one of the two intervention versions will receive a document with descriptions and contact information of additional support offers (e.g., counseling, psychotherapy, emergency room), which they can refer to in case of symptom deterioration or need for more intensive care. Additionally, participants in the GoD version will be individually referred to additional support offers by their e-coaches in case of symptom deterioration. Post-trial care will be provided for both intervention arms in form of two booster sessions unlocking automatically after 1 and 3 months, with optional guidance by an e-coach for the GoD version. Finally, participants of both intervention arms will have unrestricted access to usual treatment options (such as psychotherapy or medication).

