#### Control condition

Participants in the waitlist control group have unrestricted access to usual treatment options (TAU). They receive an information leaflet informing them about alternative support options such as university counseling services, psychotherapy, or helplines as well as the encouragement to seek help in case of any deterioration of wellbeing. After t3 (6 months after randomization), WL participants receive the unguided version of the intervention.

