### Sample size estimation

Sample size calculations refer to detect an expected increased efficacy of StudiCare-M unguided and GoD compared to WL on the primary outcome mindfulness at t2 (post-treatment). In their meta-analysis, Spijkerman et al. (2015) found a small effect for unguided mindfulness IMIs (*g* = 0.22, 95% CI 0.10–0.34) and a significantly larger effect for guided IMIs (*g* = 0.43, 95% CI 0.30–0.56) [25]. The GoD version of our IMI provides the possibility to contact an e-coach at any time. Additionally, both the GoD and unguided versions contain various persuasive e-health technologies and that have been shown to increase efficacy and adherence (e.g., self-monitoring, goal setting, SMS prompts, automatic reminders) [63, 92]. Therefore, we assume an effect size comparable to the effects previously found for guided IMIs of *d* = 0.40. Originally, a power analysis based on a two-tailed t-test (calculated using G*Power [93]) resulted in a sample size of 133 participants per group. This was documented in the first version of the trial registration. However, in the meantime, a more precise power calculation was done by an independent biostatistician (MM). This calculation indicates that 129 participants per group are required to obtain a power of 1-beta = 90% based on *α* = .05 (taking into account clustering of participants by university and assuming an ICC = .02). Trial registration was updated accordingly. As data analysis will be based on intention-to-treat (ITT) principles, increasing sample size in order to compensate for drop-outs is not necessary.

Concerning an exploratory comparison between the UG and GoD version of StudiCare-M, the sample size is sufficient to detect a small effect of *d* = 0.20 as minimal clinically important effect difference with a power of 50% and a significance level of *α* = .05. This also corresponds to the range of effect sizes of *d* = 0.02–0.33 found for different outcome measures in the trials of Berger et al. [35] and Rheker et al. [36].

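### E-coach clustering exists in the guidance-on-demand (GoD) arm only and has no place in the stated model, so standard errors for the two GoD contrasts are too small if e-coaches differ

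*Protocol article*

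**What the plan says.** **Who has an e-coach.** Under Guidance and promotion of adherence, GoD participants with questions or a wish for feedback are told that "they can contact their personal e-coach via the platform" message function. Contact of some kind reaches the whole arm: "Each participant receives a welcoming message by their e-coach as well as a short introduction how to use GoD in the first module". Beyond that, the e-coaches are "psychologists that give semi-standardized feedback on demand within 2 working days, following an e-coach manual". The same section says "Participants in the unguided version of StudiCare-M do not receive any guidance". Under Control condition, "WL participants receive the unguided version of the intervention", and only after the 6-month assessment. Up to the primary time point (8 weeks), e-coaches therefore act in one arm only.

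**What is allowed for.** Sample size estimation arrives at 129 per group, "taking into account clustering of participants by university and assuming an ICC = .02". This is the only mention of clustering in the article.

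**What is fitted.** Statistical analyses specifies linear regression for mindfulness (FMI) at 8 weeks: "Baseline and group will be defined as predictors". Secondary outcomes follow the same model. Neither university nor e-coach appears in it.

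**The concern.** Randomisation is individual, 1:1:1, so students of one university are spread over all three arms and a university effect largely cancels in a between-arm contrast. An e-coach effect cannot cancel. All participants of an e-coach are in GoD, so variation between e-coaches goes straight into the variance of the GoD mean and of every contrast that uses it. A regression on baseline and group, read as written, treats GoD participants as independent and leaves this variation out.

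At stake is GoD vs WL, one of the two contrasts for which the trial was sized: its interval could be too narrow and its p-value too small. The exploratory GoD vs UG comparison would err in the same direction. UG vs WL involves no e-coach and is not touched.

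**Working it through.** **Inputs from the article.** 129 per group, d = 0.40, alpha .05 (the original calculation was two-tailed), power 90%, university ICC .02.

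**Inputs that are assumptions.** Number of e-coaches k (3 to 15), equal caseloads m = 129/k, and e-coach ICC (.01 to .05). The article gives none of these.

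**Step 1: reproduce the plan's figure.** The normal-approximation sample size per group is 2 × ((1.960 + 1.282)/0.40)² = 131.34. Multiplying by (1 − .02), the factor for individual randomisation within universities, gives 128.7, rounded up to 129. The stated figure is reproduced and contains no e-coach term. Before any e-coach effect, power at 129 per group is Φ(0.40/√(2/129) − 1.96) = 89.5%.

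**Step 2: add clustering in GoD alone.**
- Design effect in the GoD arm: DE = 1 + (m − 1) × ICC
- True standard error relative to the model's: r = √((1 + DE)/2)
- Actual error of a nominal two-sided 5% test: 2 × (1 − Φ(1.96/r))
- Power at d = 0.40 with the correct standard error: Φ(0.40/√((1 + DE)/129) − 1.96)

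Worked example with 5 e-coaches and ICC .02: m = 25.8; DE = 1 + 24.8 × .02 = 1.496; r = √(2.496/2) = 1.117; error = 2 × (1 − Φ(1.755)) = 7.9%; power = Φ(0.40/0.1391 − 1.96) = 82.0%.

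| E-coaches | ICC | DE in GoD | SE ratio | Actual error | Power at d = 0.40 |
|---|---|---|---|---|---|
| any | 0 | 1.00 | 1.00 | 5.0% | 89.5% |
| 15 | .01 | 1.076 | 1.02 | 5.4% | 88.4% |
| 10 | .01 | 1.119 | 1.03 | 5.7% | 87.7% |
| 10 | .02 | 1.238 | 1.06 | 6.4% | 85.9% |
| 5 | .02 | 1.496 | 1.12 | 7.9% | 82.0% |
| 5 | .05 | 2.240 | 1.27 | 12.4% | 71.4% |
| 3 | .05 | 3.100 | 1.43 | 17.1% | 61.2% |

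The standard error ratio and the error rate apply equally to GoD vs UG, since UG also has no e-coach clusters.

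**The case against.** The strongest reply is that the size comes from outside the document. Neither caseload nor e-coach ICC is stated, and the 17% error needs very few e-coaches and a fairly high ICC together. This stands: the table shows a range of possibilities and does not estimate what will happen in this trial.

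The article also points to the low end. Apart from the welcome message, contact takes place only when the participant asks for it. Feedback is semi-standardised and manual-based, and it comes from trained, supervised psychologists. Module content, automated reminders and text messages do not depend on the e-coach. The Introduction adds that the two earlier GoD trials found no significant difference in efficacy or adherence from unguided versions. This too stands, although none of it makes the ICC zero. The sample size section itself cites e-coach access in support of the assumed d = 0.40.

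A third reply is that the model sentence is condensed and that an analysis plan not shown may add random effects or robust standard errors. That is possible. But the article names the predictors and raises clustering itself, for a source that largely cancels between arms and not for the one that cannot.

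Two stronger readings are tempting and not supported:
- A reader might take .02 as the plan's ICC for e-coaches and so treat 7.9% error and 82% power as the plan's own consequence. The .02 is a university ICC; the article states no e-coach value.
- A reader might conclude that the GoD claim should rest on the e-coach model in place of the stated one. With 3 to 5 e-coaches the between-coach variance has only about 2 to 4 degrees of freedom and may be estimated as zero or erratically. Whether e-coaches are a random sample or part of the intervention as delivered is also a choice of inference target. That is too weak a basis for replacing the primary analysis.

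**Conclusion.** The structural point holds. GoD participants are nested in e-coaches, the other arms are not, and the stated model ignores it. Any positive e-coach ICC makes the standard errors of GoD vs WL and GoD vs UG too small; at an ICC of zero nothing changes.

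Under the assumed 3 to 15 equal caseloads and ICC .01 to .05, the true standard error is 1.02 to 1.43 times the model's, with actual error of 5.4% to 17%. The on-demand, manual-based contact makes the lower part of that range more likely. The documents do not show that the GoD result will be wrong, only that the plan has no check on whether its interval is wide enough. The point calls for a cheap improvement and does not invalidate the primary analysis.

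**What to change.** Keep the stated primary model. In addition:

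1. Record an e-coach identifier for every GoD participant.
2. Pre-specify, for GoD vs WL and GoD vs UG, a sensitivity analysis as a partially nested mixed model: baseline and group as in the primary model, a random e-coach effect in GoD only, arm-specific residual variance, and small-sample degrees of freedom.
3. Report the number of e-coaches and the estimated e-coach ICC.
4. Release the identifier only after the blinded primary analysis is locked. It would be filled in for GoD alone and would reveal that arm to the analyst, who under Statistical analyses and Data Availability works on blinded data.
5. Qualify the GoD conclusion if the two intervals differ materially.

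All analyses are to follow completion of data collection, so this can be laid down before results are seen. The cost is one extra model and retrieval of the e-coach assignments. The variance estimate will be imprecise if e-coaches are few, and the GoD interval may come out wider.

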Finally, the questions of how and for whom exactly mindfulness-based IMIs (as well as IMIs in general) work are yet to be answered [25, 37]. As large-scale RCTs provide an excellent framework for moderation and mediation analyses, they should routinely incorporate such analyses [38]. Therefore, in the current study, we will exploratively examine various potential moderating variables such as sociodemographic variables, pre-treatment symptomatology and treatment expectancy. From theory and current evidence, we also deduced a number of potential variables mediating the effect of mindfulness IMIs on mental health. Those include mindfulness itself [39], cognitive fusion as an aspect of psychological flexibility [39, 40], emotion regulation [41] and clarity about one’s internal experience (operationalized via alexithymia) [42]. Additionally, we will look at self-efficacy, as empowerment and self-management are assumed to be crucial factors for the efficacy of self-help interventions [43].

The current study is an extension of a previous RCT that investigated the efficacy and acceptance of *StudiCare Mindfulness* (StudiCare-M), a guided internet-based intervention to enhance mindfulness and wellbeing in college students [44]. We will examine whether an adapted unguided as well as a GoD version can be effective, as these would offer affordable options for long-term implementation into student health promotion programs. The specific research questions are:
Are the unguided and GoD versions of StudiCare-M effective in enhancing mindfulness in college students compared to a waitlist control group?Are these two versions also effective concerning the secondary outcomes depression, anxiety, stress, presenteeism, well-being and interoceptive sensibility?Are the unguided and GoD versions of StudiCare-M associated with side effects or adverse events?Are there any differences between the unguided and GoD version of StudiCare-M concerning efficacy, adherence, satisfaction, side effects, or adverse events?Which factors are associated with, moderate or mediate the effects of StudiCare-M?

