**Covariates**						
Demographic variables	SRQ		x			
Previous experience with mindfulness, use of additional treatment options	SRQ		x		x	x
Treatment expectation	CEQ		x			

*Note.*
*CEQ* Client Expectancy Questionnaire, *CFQ-D* Cognitive Fusion Questionnaire, *CSQ-8* Client Satisfaction Questionnaire, *German Version* ZUF-8, *ERQ* Emotion Regulation Questionnaire, *FMI* Freiburg Mindfulness Inventory, *GAD-7* Generalized Anxiety Disorder Questionnaire, *INEP* Inventory for the Assessment of Negative Effects of Psychotherapy, *BPQ* Body Perception Questionnaire, Awareness Section, *PHQ-9* Patient Health Questionnaire, *PSS* Presenteeism Scale for Students, *PSS-4* Short Form Perceived Stress Scale, *SES* Self-Efficacy Scale, *SRQ* Self-Report Assessment Questionnaire, *TAS-20* Toronto-Alexithymia Scale, *WHO-5* World Health Organization Well-Being Index

*Intervention groups only (UG, GoD)

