This is one of few studies that examine the effect of “guidance on demand” (GoD) on adherence and efficacy of internet-based interventions [35, 36] and the very first to do so for a mindfulness IMI. As discussed before, mindfulness IMIs could provide an excellent possibility to reach students in need on a population level. Guided IMIs have shown to be most effective but can be associated with increased intervention costs [32]. Consequently, it is worth investigating whether a GoD-IMI for enhancing mindfulness can be effective and well accepted by participants. Additionally, we will compare GoD to an unguided version of StudiCare-M on an exploratory level. Both versions of our intervention are designed according to principles of persuasive design. Therefore, we will gather preliminary evidence on differences between persuasively designed unguided IMIs and IMIs with a minimal form of human guidance concerning effectiveness, adherence, side effects, and adverse events.

While the efficacy of mindfulness IMIs has been shown in many RCTs by now, the questions of how and for whom these interventions work have not been answered sufficiently. Therefore, this RCT will examine a range of different moderators and mediators on an exploratory level in order to contribute to this still understudied area of research [25]. Trials investigating mediators often suffer from methodological limitations such as measuring the proposed mediators, dependent and independent variables only pre- and post-treatment. Consequently, they are unable to establish chronology of change, therefore neglecting a crucial element of investigating mediators [98]. We aim to overcome this shortcoming by conducting an additional assessment at midpoint of the intervention, enabling us to find out at what time changes occur.

One last strength of this RCT is the fact that we will measure potential side effects and adverse events. It has been shown that IMIs can have negative side effects [103–105], but those have been understudied so far [104]. This is especially the case for mindfulness IMIs, where no study so far has investigated such effects. This RCT will therefore contribute to our knowledge on the safety of minimally or unguided mindfulness IMIs, an important precondition for a possible large-scale dissemination of such interventions in the future.

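### The individual-level harm analysis (reliable deterioration) names no scale, reads as mindfulness only, and states no comparison with the waitlist

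*Protocol article*

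**What the plan says.** Research question 3 in the Introduction asks: "Are the unguided and GoD versions of StudiCare-M associated with side effects or adverse events". The Discussion counts this among the trial's strengths, saying the trial will "contribute to our knowledge on the safety of minimally or unguided mindfulness IMIs".

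Three parts of the plan bear on that question:

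- **Reliable deterioration.** Statistical analyses first sets out the responder analysis: "To obtain the number of participants achieving reliable improvement in mindfulness (FMI), participants will be coded as responders and nonresponders", using the RCI at t2 and t3. The next sentence turns to harm in single participants and gives the method as "calculating the number of participants that display a reliable deterioration from t0 to t2 and t3 also using the RCI". It names no outcome scale and no comparison between arms.
- **INEP.** The adapted 22-item inventory is collected at t2 and t3. Table 2 marks it with an asterisk, which the note below explains as "Intervention groups only (UG, GoD".
- **Symptom scales.** Table 2 lists PHQ-9 and GAD-7 at t0, t1, t2 and t3, with no restriction by arm. They are analysed like the primary outcome, by linear regression on baseline and group, with standardized mean differences and 95% CIs.

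A concurrent untreated control exists at both time points. Under Control condition: "After t3 (6 months after randomization), WL participants receive the unguided version of the intervention".

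**The concern.** Two things are left open in the one analysis meant to detect harm in individuals.

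**The scale.** Read in sequence, the deterioration sentence carries on from the FMI responder sentence. The FMI is the construct the intervention is built to raise, so a fall in FMI is an indirect signal of harm. A participant whose depression or anxiety reliably worsens while mindfulness holds steady or rises would not be counted. The expected benefit on FMI would itself lower the count in the active arms. Elsewhere (Guidance and promotion of adherence; Control condition) the article's own worry is worsening of symptoms or wellbeing.

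**The comparator.** Some participants will cross a deterioration threshold without any intervention. Research question 3 is about association, and a number of deteriorated participants says nothing about that unless it is set against the waitlist rate.

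At stake is whether the trial can report a controlled, individual-level estimate of symptom harm. A favourable mean difference can coexist with a minority who get worse, which is the usual reason for adding an individual-level analysis.

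**Working it through.** The article gives no figure for the deterioration analysis, so there is none to reproduce. Its sample size sets the precision and can be recovered: 2 × ((1.960 + 1.282)/0.40)² = 131.3 per group for d = 0.40, 90% power and two-sided α = .05. The exact t-test version gives 133, the article's original figure. Multiplying 131.3 by (1 − 0.02) gives 128.7, so 129. That factor is an inferred way of using the stated ICC; the article gives no formula.

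**1. RCI thresholds, from the article's reliabilities.** Threshold in baseline SD units = 1.96 × √(2 × (1 − α)).

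- FMI, α = 0.84: 1.96 × √0.32 = 1.11 SD
- PHQ-9 and GAD-7, α = 0.89: 1.96 × √0.22 = 0.92 SD

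**2. What an FMI-only count could miss (illustration; the correlations are assumptions).** Change scores on both scales are taken as bivariate normal, with SD √(2(1 − r)) in baseline SD units. Here r is the t0–t2 correlation of each scale (assumed 0.5 to 0.7). The correlation between FMI worsening and PHQ-9 worsening is assumed to be 0.3 to 0.7. The missed share is 1 − P(both deteriorate)/P(PHQ-9 deteriorates). The last column assumes mean improvement of 0.40 SD on FMI (the plan's d) and 0.30 SD on PHQ-9 (assumed).

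| r | PHQ-9 deteriorated, no mean change | FMI deteriorated, no mean change | Missed, no mean change | Missed, with improvement |
|---|---|---|---|---|
| 0.5 | 17.9% | 13.4% | 55–76% | 66–85% |
| 0.6 | 15.2% | 10.8% | 59–79% | 71–88% |
| 0.7 | 11.8% | 7.6% | 64–83% | 77–92% |

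These shares apply only if the count is on FMI alone.

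**3. Background rate without intervention.** Measurement error alone puts 2.5% beyond the threshold in the worse direction: 0.025 × 129 = 3.2 participants. Under the assumptions of step 2 with no mean change, reliable PHQ-9 deterioration on the waitlist would be 11.8% to 17.9%, or about 15 to 23 of 129. An active-arm count of that size could be entirely natural worsening.

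**4. Precision of a waitlist contrast.** Half-width = 1.96 × √(2p(1 − p)/129), with all 129 per arm contributing.

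- p = 5%: 1.96 × √(0.095/129) = 5.3 points
- p = 10%: 1.96 × √(0.18/129) = 7.3 points
- p = 15%: 1.96 × √(0.255/129) = 8.7 points

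For example, 13/129 against 6/129 gives +5.4 points (Newcombe 95% CI −1.1 to +12.3). With 80% power at two-sided .05, the detectable rises are from 5% to about 16%, or from 10% to about 23%. The contrast is usable as an estimate, not as a powered safety test.

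**The case against.** The other side has real substance.

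- **FMI is not stated.** The deterioration sentence turns from response to harm and cites different sources from the responder sentence. What it carries over explicitly is the method. Since the article otherwise speaks of deterioration in symptoms or wellbeing, a symptom scale may have been meant. This stands: the defect is an unnamed scale, with FMI as the reading the text invites.
- **Silence is not exclusion.** The count covers participants without limiting it to the active arms, and this is a three-arm trial against waitlist. A reader might infer that comparison with the waitlist is ruled out; nothing says so. A full protocol or analysis plan, not shown, may add it.
- **Other analyses bear on safety.** Mean PHQ-9 and GAD-7 are already compared by arm. The INEP asks about effects attributed to the intervention, so restricting it to treated participants is reasonable. A reader might infer that research question 3 cannot be answered at all; that goes too far. Still, means do not show who worsened, and the INEP has no control.
- **The missed shares are modelled.** A reader might take it as established that the plan misses most symptom worsening. That holds across the assumed range only on the FMI-only reading, and it is not a figure from the article.
- **Missing data.** Intention-to-treat analysis with imputation is already planned, and nothing suggests drop-outs would be counted as not deteriorated.

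The appeal to detail held elsewhere does not dispose of the point. The article does specify this harm analysis and, in doing so, points to the intervention's own target scale and to a bare count.

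**Conclusion.** The point holds in limited form. As written, the plan specifies no controlled individual-level analysis of symptom harm: the deterioration scale is unnamed and reads as FMI, no waitlist contrast is stated, the INEP has no waitlist data, and the regressions address means. The article does not show that the waitlist is excluded, that the safety question is unanswerable, or what share of worsening would go uncounted.

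The firm figures are the thresholds (1.11 SD for FMI, 0.92 SD for PHQ-9 and GAD-7, from the stated reliabilities) and, for an assumed 10% rate with complete data, a half-width of about 7 points. The missed shares and background rates rest on assumed correlations and normality, and serve only to show that the choice of scale and comparator matters.

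No primary result or sample size is affected. This is an inexpensive improvement that should be made.

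**What to change.** In Statistical analyses, state that:

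- reliable deterioration will be computed for PHQ-9 and GAD-7 as well as FMI, from t0 to t2 and from t0 to t3, in all three arms;
- each active arm will be compared with the waitlist as a risk difference with 95% CI;
- missing data will be handled as in the primary analysis;
- these are descriptive safety estimates without significance claims, to be read alongside the active-arm INEP when answering research question 3.

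The cost is a few lines of text and some extra tables from data already collected. The downside is a handful of additional, imprecise descriptive estimates: an interval that includes zero should not be reported as evidence of no harm.
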